#### Secondary endpoints analysis

Mortality is an intercurrent event that could potentially occur before observation of many of the secondary endpoints in this trial in addition to the primary endpoint. Most secondary outcomes will involve evaluation of the intervention effect to be expected in infants while alive. Analysis of secondary endpoints will be performed on the intention-to-treat set of all randomised infants. The exceptions to this are

- Number of attempts taken to successfully intubate in the delivery room – will only be assessed for those who need to be intubated in the delivery room (intubation in the delivery room is indicated by variable **dr\_infant\_intub.factor**)
- Rectal temperature on admission to NICU as well as NICU intubation will only be evaluated for infants who are admitted to NICU alive (identified by derived variable **nicu\_admission**)

|         |                                           |              |               |
|---------|-------------------------------------------|--------------|---------------|
| UCD CRC | SAP for the POPART trial                  |              |               |
| UCD CRC | Template: Statistical Analysis Plan (SAP) | Version: 1.0 |               |
|         |                                           |              | Page 13 of 19 |

- Bronchopulmonary dysplasia (BPD) – supplemental O2 at 28 days of life - will only be evaluated for infants who are alive at 28 days of life (infants alive at 28 days to be determined by the variable **bpd\_d28.factor** )
- Chronic lung disease of prematurity (CLD), the need for supplemental O2 at 36 weeks corrected gestational age (CGA) determined by physiological oxygen reduction test - will only be evaluated for infants who are alive at 36 weeks CGA (determined by the variable **cld\_36wks.factor** )
- Duration of hospitalisation will be summarized and analyzed both for infants who survive to hospital discharge and for the whole sample. A similar approach will be used for days of mechanical ventilation and days of respiratory support.

Each categorical secondary endpoint will be analysed using the same approach as the main analysis of the primary endpoint.

For the time-to-event endpoint death before hospital discharge, Kaplan-Meier curves will be constructed to visualize the pattern of mortality over the study period, with median survival time reported with 95% confidence intervals. Cox proportional hazards regression will be used to quantify the hazard ratio for those treated with oropharyngeal surfactant vs standard-of-care. A Cox proportional hazards regression model will also be fitted to determine sensitivity of the estimated intervention effect to potentially relevant covariates; including centre, gestational age, birth weight, gender, mode of delivery (vaginal versus caesarean birth) and antenatal corticosteroid treatment.

Each numeric secondary endpoint (e.g. duration of mechanical ventilation, duration of hospitalisation), will be analysed using the following approach.

- Descriptive statistics will be calculated to compare the endpoint across treatment groups. This will include the frequency of missing data per treatment arm, minimum and maximum values, mean and standard deviation for symmetrically distributed variables and median and interquartile range for asymmetrically distributed variables. The difference in means (or medians where relevant) between treatment groups will be presented with a 95% confidence interval. Confidence intervals for the difference in means will use a Normal approximation while confidence intervals for the difference in medians will be calculated by bootstrap resampling.
- A superiority hypothesis test (two-sided independent sample t-test) will be carried out to test for a difference in means between control and intervention. Alternatively, if t-test assumptions are not valid, a Mann-Whitney U test will be carried out to test for a difference in the the endpoint between control and intervention.

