### 14.2 Determination of sample size subjects

In randomised studies, the rate of mechanical ventilation in the days after birth among preterm infants treated with CPAP alone has varied from 46– 60%. (2, 11, 19-21) Minimally invasive surfactant techniques were shown to reduce the rate of mechanical ventilation to from 46% to 28% in a cohort of infants with a gestational age between 26 and 28 weeks. (21)

Sample size for this study was calculated in G\*power, using a two-sided, two-proportion Z test. To detect a difference in the rate of endotracheal intubation for respiratory failure of 18% between treatment arms (assuming a rate of 46% in the control group and 28% in the intervention arm) with 80% power and a 5% significance level, a sample size of 224 infants would be required. To compensate for a death rate of 10% (estimated from local data, The National Maternity Hospital, Neonatal Clinical Report for 2015) before the primary outcome can be determined (i.e. at 120 hours), we will need to recruit a total of **250** infants to this study.

The National Maternity Hospital is a stand-alone university maternity hospital with a tertiary NICU to which > 150 infants < 1500g are admitted annually. We have a track record of initiating, conducting, completing, presenting and publishing investigator-led randomised controlled trials, including trials that compared delivery room interventions, (12-14) trials that had respiratory failure in the NICU as the primary outcome (15) and trials that compared investigational medicinal products (16) in preterm infants. Though the enrolment rates to our studies amongst eligible infants are consistently excellent (> 80%), we believe it will be necessary to enrol infants at multiple sites in order to enrol our planned target sample of 250 infants in a timely fashion. We have a track record enlisting the help of collaborators

nationally(16)andinternationally(14, 17)to perform our studies. We believe that with their help, we can enrol these infants in 2–3 years.

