| UCD CRC | SAP for the POPART trial |  |
|---------|--------------------------|--|

|         |                                           |              |              |
|---------|-------------------------------------------|--------------|--------------|
| UCD CRC | Template: Statistical Analysis Plan (SAP) | Version: 1.0 |              |
|         |                                           |              | Page 6 of 19 |

- Incidence of cystic periventricular leukomalacia (**cystic\_pvl.factor**)
  - Evidence on surveillance cranial ultrasounds performed regularly in NICU as standard of care
- Retinopathy of prematurity treated with laser photocoagulation or intravitreal injections (**retinopathy\_tr\_req.factor**)
  - Evidence on surveillance ophthalmology review performed regularly in NICU as standard of care
- Death before hospital discharge ( **hospitalisation\_death.factor** )
- Survival without BPD at hospital discharge ( **without\_bpd\_at\_discharge.factor** )
- Survival without CLD at hospital discharge ( **without\_cld\_at\_discharge.factor** )
- Duration of hospitalisation ( **hospitalisation\_duration** )
- Use of home oxygen therapy (**home\_oxygen.factor**)
  - Discharged home on oxygen therapy

These are clearly defined outcome measures and will be recorded during the infants hospital stay prior to discharge home from hospital. These outcome measures include complications of prematurity that can occur at any stage from birth until discharge home and thus specific timeframes for measurement is not applicable in all cases.

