### 5.3 Missing data

All data will be checked for missing values and followed-up to obtain data where possible. Missing data will be summarised by variable and by treatment arm. Spurious or anomalous data will also be queried and corrected if found to be incorrect. No data will be excluded as outliers.

For the handling of missing data, we will follow the flowchart given in . If there is few (<5%) or a lot (>40%) of missing data, we will only use the observed data for the analysis.

With a low frequency of missing data (<5%), we will also perform worst case/best case sensitivity analysis for the study endpoints.

With missingness between 5 and 40% missing data will be replaced using multiple imputation. Multiple imputations will be based on the randomization arm, and selected baseline, procedural and outcome variables (see below for selection criteria). Since missing values in these variables are possible, chained equations will be used (e.g. using mi impute chained in Stata or the mice package in R^4). This procedure fills in missing values in multiple variables iteratively based on a sequence of univariate imputation methods with fully conditional specification of prediction equations. Predictive mean matching will be used for continuous, logistic regression for binary, ordinal logistic regression for ordinal and multinomial regression for categorical variables (if applicable). Based on such chained equations, a total of 50 multiple imputations will be calculated. If it is not possible to impute all outcomes in one model, a stepwise approach will be considered. The 50 imputed data sets will be analysed using Rubin's rules.

Variables will be selected for inclusion in the imputation model using the following principles:

- Variables with more than 40% missing values will not be used
- Binary variables with a frequency of less than 5% in one category will not be used
- If two binary variables have less than 5% or more than 95% discordant pairs only one of the two will be used (the one with less missings).
- Levels of ordinal variables with a frequency of less than 5% will be collapsed by adding the entries to the neighbouring category (i.e. next higher or lower level) with the higher frequency (if there are more than one).
- Categorical variables might generally be recoded if it improves the fit of the imputation model and does not lead to substantial loss of information.

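### Home oxygen is analysed over all randomised infants, so a death before discharge counts as no home oxygen, although BPD and CLD are restricted to infants alive at assessment

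*Combined protocol and SAP*

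**What the plan says.** SAP 5.1.1, under secondary endpoints analysis, first recognises that death can come before many secondary endpoints are observed. It says: "Most secondary outcomes will involve evaluation of the intervention effect to be expected in infants while alive". It does not say which outcomes fall outside that majority. It then fixes the population: "Analysis of secondary endpoints will be performed on the intention-to-treat set of all randomised infants".

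The listed exceptions are:
- delivery-room intubation attempts (only infants intubated there);
- rectal temperature on admission and NICU intubation (only infants admitted alive);
- BPD, which "will only be evaluated for infants who are alive at 28 days of life";
- CLD, which "will only be evaluated for infants who are alive at 36 weeks CGA";
- the durations, shown two ways: "Duration of hospitalisation will be summarized and analyzed both for infants who survive to hospital discharge and for the whole sample", with a similar approach for days of ventilation and of respiratory support.

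Home oxygen is not listed. SAP 1.3 defines it as "Discharged home on oxygen therapy", and Protocol 11.4 groups it with the data that depend on discharge. Categorical secondary endpoints follow the method of the primary endpoint, and SAP 5.1.1 scores the primary endpoint in infants who die early on the time they were alive.

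On incomplete data, SAP 5.3 says: "With missingness between 5 and 40% missing data will be replaced using multiple imputation". Below 5% or above 40%, only observed data are used; below 5% a best-case/worst-case analysis is added. The section does not separate values that are missing from values that do not exist because the infant died.

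**The concern.** An infant who dies in hospital can never go home on oxygen. Keeping that infant in the denominator as a non-event lets death score as the favourable result. The SAP avoids this for the two sister lung outcomes by restricting them to infants alive at the assessment time. Those two also have companion endpoints over all randomised infants (survival without BPD and survival without CLD at discharge). Home oxygen has neither a survivor denominator nor a composite, although discharge comes after day 28 for most of these infants and so leaves at least as much time for deaths to intervene.

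Two things are at stake. The home-oxygen rate would be lower than the rate among survivors, and would sit beside BPD and CLD rates built on a different principle. If mortality differs between arms, the relative risk and the Z test for home oxygen would partly measure mortality, with the sign reversed.

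**Working it through.** **The plan's own figure.** The documents give no planning figure for home oxygen. The only mortality figure is the 10% in Protocol 14.2, assumed to die before the primary outcome can be determined at 120 hours. It enters the sample size as follows:
- 46% v 28%, two-sided 5%, 80% power, pooled-variance Z test: n per arm = [1.96·√(2 × 0.37 × 0.63) + 0.842·√(0.46 × 0.54 + 0.28 × 0.72)]² / 0.18² = 111.8, so 112 per arm and 224 in total (power 0.801).
- 224 / 0.90 = 248.9, stated as 250.

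Both figures reproduce, and neither depends on the home-oxygen rule.

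**Inputs for the check.** Mortality of 10% is the planning figure, and mortality to discharge cannot be below mortality to 120 hours. Mortality of 15% or 20%, all differences between arms, and the 30% home-oxygen rate among survivors are assumptions for illustration.

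**Route 1: deaths counted as no home oxygen.** Let s be the rate among survivors and m the mortality before discharge.
- Rate over all randomised = s × (1 − m). The ratio to the survivor rate is 0.90 at m = 10%, 0.85 at 15% and 0.80 at 20%. With s = 30%, the reported rate is 27.0%, 25.5% or 24.0%.
- With the same s in both arms, relative risk (surfactant v control) = (1 − m_surfactant) / (1 − m_control), whatever the value of s.

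| Mortality, control v surfactant | Rates over all randomised (s = 30%) | Relative risk | Survivor relative risk |
|---|---|---|---|
| 10% v 10% | 27.0% v 27.0% | 1.00 | 1.00 |
| 10% v 15% | 27.0% v 25.5% | 0.85/0.90 = 0.94 | 1.00 |
| 10% v 20% | 27.0% v 24.0% | 0.80/0.90 = 0.89 | 1.00 |
| 20% v 10% | 24.0% v 27.0% | 0.90/0.80 = 1.13 | 1.00 |

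A real excess can also be hidden. With survivor rates of 30.0% v 33.75% (relative risk 1.125) and mortality of 10% v 20%, the rates over all randomised are 0.300 × 0.90 = 27.0% and 0.3375 × 0.80 = 27.0%, a relative risk of 1.00.

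**Route 2: field left blank for deaths.** At 10% mortality, 25 of 250 infants have no value; at 20%, 50 of 250. Both fall in the 5–40% band, so SAP 5.3 as written leads to imputing a discharge status for infants who died. If q is the imputed rate, the rate per arm is s(1 − m) + q·m. With s = 30% and mortality 10% v 20%:
- q = 20%: 29% v 28%, relative risk 0.97
- q = 30%: 30% v 30%, relative risk 1.00
- q = 40%: 31% v 32%, relative risk 1.03
- q = 60%: 33% v 36%, relative risk 1.09

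The direction depends on q, and q has no true value to aim at.

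**Route 3: blanks below 5%.** Deaths would be dropped from the main analysis, but the best-case/worst-case analysis would still assign them values. At the 10% planning figure this route would not be reached.

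**The case against.** The best defence is that the all-randomised rate is a legitimate quantity. An infant who died was indeed not discharged on oxygen, the set respects randomisation, and restriction to survivors conditions on something that happens after randomisation. That is true, and the rate is too low only when judged against the survivor rate. But the survivor rate is what the SAP itself chose for BPD and CLD, and it gives no reason for treating home oxygen differently.

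It can also be said that SAP 5.1.1 handles death as an intercurrent event, so imputation for deaths was never intended. That may be so. SAP 5.3 does not say it, and the imputation route is a gap in the wording rather than a stated intention.

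Mitigation exists. Death before discharge has its own Kaplan-Meier and Cox analysis, and SAP 5.4 reports deaths by arm, so a reader could largely rebuild a survivor denominator. A gap of 10% v 20% with 125 per arm would itself be visible (z about 2.2, p about 0.03), and a relative risk of 0.89 at s = 30% would carry a 95% interval of about 0.58 to 1.36. These points limit the damage but do not correct the home-oxygen estimate.

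Three stronger readings are tempting and are not supported:
- *Imputation also understates the rate and favours the arm with more deaths.* It does not do so reliably; Route 2 goes either way.
- *The treatment comparison is necessarily biased.* With equal mortality the relative risk is unchanged, and the documents give no mortality by arm.
- *Treated retinopathy has the same fault.* Treatment is given in hospital and can precede a later death, so a while-alive rate over all randomised infants is coherent. The documents also do not show that attendance at eye review is captured to define another denominator.

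**Conclusion.** The point holds for home oxygen. The stated analysis set, read with the while-alive scoring of deaths, counts each death before discharge as no home oxygen, which conflicts with the SAP's own handling of BPD and CLD. The reported rate is about 10% below the survivor rate, in relative terms, at 10% mortality, and further below if more infants die between 120 hours and discharge. The relative risk is distorted only if mortality differs between arms.

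Two assumptions carry this. The 10% is a planning figure, which the protocol synopsis describes instead as loss to follow-up. The arm-specific mortality rates are illustrative. If deaths are left blank instead, the fault is an undefined value that would be imputed, with no fixed direction. One secondary endpoint is affected; the primary analysis, the sample size and the interim stopping rule are not.

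**What to change.** - **SAP 5.1.1:** add home oxygen to the exceptions, evaluated among infants who survive to discharge. Survivors still in hospital at the Protocol 11.4 cut-off should stay in the denominator, using the oxygen status recorded there (one month beyond the expected date of delivery). A denominator limited to infants already discharged home could lose long-stay survivors, including those still on oxygen.
- **Results table:** report death or home oxygen over all randomised infants beside the survivor rate.
- **SAP 5.3:** state that values undefined because of death are not missing data, are not imputed, and do not count towards the 5% and 40% thresholds.

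The cost is a few lines of SAP wording and one extra table row. Death, home oxygen and the long-stay oxygen status are already to be recorded, so no new data are needed. The downside is that the survivor denominator conditions on a post-randomisation event. The SAP already accepts this for BPD and CLD, and the composite covers it. If the database is already locked, the change should be described and justified in the final report, as Protocol 14.10 requires for deviations.

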### 2.2 Framework for analysis

|         |                                           |              |
|---------|-------------------------------------------|--------------|
| UCD CRC | SAP for the POPART trial                  |              |
| UCD CRC | Template: Statistical Analysis Plan (SAP) | Version: 1.0 |
|         |                                           | Page 8 of 19 |

Analysis of efficacy endpoints will be carried-out following the Intention-To-Treat (ITT) principle. A Per Protocol analysis will also be carried out on the primary endpoint for sensitivity analysis. For all statistical analysis, a p-value < 0.05 will be considered statistically significant.

Interim analysis of the primary endpoint and the important secondary endpoint, death before hospital discharge, will be performed by an external data safety monitoring board. This will be performed once half the planned sample (126 participants) have completed the trial.

For the primary analysis of the primary endpoint, a superiority hypothesis test (two-sided, two-proportion Z test) will be carried out to investigate whether the rate of endotracheal intubation differs between intervention and standard-of-care. In this analysis, infants intubated for signs of respiratory failure will be considered to have met the primary endpoint.

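### In the whole-sample comparisons of hospital stay and respiratory-support days, an early death counts as a short duration, so a mortality difference can favour the arm with more deaths

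*Combined protocol and SAP*

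**What the plan says.** SAP 5.1.1 (Secondary endpoints analysis) recognises the difficulty: "Mortality is an intercurrent event that could potentially occur before observation of many of the secondary endpoints in this trial". Its general answer is a while-alive approach: "Most secondary outcomes will involve evaluation of the intervention effect to be expected in infants while alive". For hospital stay it then specifies two populations: "Duration of hospitalisation will be summarized and analyzed both for infants who survive to hospital discharge and for the whole sample". It adds: "A similar approach will be used for days of mechanical ventilation and days of respiratory support".

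The same section sets the test for numeric endpoints: "A superiority hypothesis test (two-sided independent sample t-test) will be carried out to test for a difference in means between control and intervention". The fallback reads: "if t-test assumptions are not valid, a Mann-Whitney U test will be carried out". SAP 2.2 sets the threshold: "For all statistical analysis, a p-value < 0.05 will be considered statistically significant".

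Neither population is named as the main analysis for the three durations. Neither document gives infants who die a fixed value or rank, uses days alive and free of support, or treats death as a competing event for these endpoints. The competing-risks model in SAP 5.1.2 covers only the primary endpoint. Protocol 11.4 has a rule for very long stays (censoring six months after the expected date of delivery), but there is no matching rule for stays cut short by death.

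**The concern.** If duration is counted while the infant is alive, a death on day 2 enters the whole-sample comparison as about 2 days of stay and at most about 2 days of respiratory support. Among infants born before 29 weeks, almost every survivor will have a longer value. Shorter is read as better, so each early death pulls its arm towards apparent benefit.

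Death is not rare here. Protocol 14.2 plans for 10% of infants dying before 120 hours, and death before discharge is singled out as an important secondary endpoint. If surfactant changed mortality, the whole-sample duration result would be pushed in the opposite direction to the mortality result, yet would carry its own superiority p-value. Harm through death could then be reported as a shorter stay, or a survival gain as a longer one.

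**Working it through.** **The plan's own figures.** The documents give no calculation for the durations. The sample size, which fixes the number per arm, reproduces: 46% vs 28%, two-sided 5%, 80% power gives 112 per arm, or 224 (power 80.1%). Then 224 / 0.9 = 248.9, rounded up to 249, against the stated 250. Allocation is 1:1 (protocol 11.3.6), so 125 per arm.

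**Formula.** Let p be mortality, S the mean duration in survivors and D the mean in infants who die. An arm's whole-sample mean is (1 − p)S + pD. With S and D the same in both arms, the difference (arm with more deaths minus the other) is

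−(p₂ − p₁)(S − D).

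It is negative whenever S exceeds D, although survivors have identical durations.

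**Hospital stay, main scenario (assumptions).** Survivor stay is lognormal, median 85 days, log-SD 0.3, so S = 85 × exp(0.045) = 88.9. Time to death is lognormal, median 5 days, log-SD 1, so D = 5 × exp(0.5) = 8.2. S − D = 80.7.

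- 10% vs 20%: −0.10 × 80.7 = −8.1 days.
- 10% vs 15%: −0.05 × 80.7 = −4.0 days.

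Simulated trials with 125 per arm and a two-sided test at 0.05 gave the following. By chance, 2.5% would favour the arm with more deaths.

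| Mortality | Mean difference | t-test favours arm with more deaths | Mann-Whitney favours arm with more deaths |
|---|---|---|---|
| 10% vs 15% | about −4 days | 15% | 11% |
| 10% vs 20% | about −8 days | 38% | 26% |

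With equal mortality there was no bias. At 10% vs 12%, 4.1% of Mann-Whitney tests favoured the arm with more deaths.

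**Hospital stay, other shapes.** With gamma survivor stay of mean 80 to 100 days and exponential time to death of mean 5 to 15 days:

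- 10% vs 20%: from −0.10 × (80 − 15) = −6.5 to −0.10 × (100 − 5) = −9.5 days; 34–40% (t-test) and 25–27% (Mann-Whitney).
- 10% vs 15%: −3.25 to −4.75 days; 13–15% and 10–11%.

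**Respiratory support.** Survivor mean 50 days, mean 5 days in deaths, 10% vs 20%: −0.10 × 45 = −4.5 days; 26% (t-test) and 29% (Mann-Whitney).

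**Ventilation days, 10% vs 20%.** Protocol 14.2 cites ventilation rates of 46–60% in the days after birth on CPAP alone, so 40–54% were not ventilated in that period. An infant ventilated until an early death can rank worse than all survivors who were never ventilated.

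- Survivor mean 10.5 days, deaths 2 to 5 days: −0.85 to −0.55 days; only 5–7% (t-test) and 2–4% (Mann-Whitney) favour the arm with more deaths.
- Survivor mean 4 days, deaths 5 to 15 days: +0.1 to +1.1 days, so the sign reverses.

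**Ranking deaths worst.** In the gamma scenarios for stay at 10% vs 20%, Mann-Whitney results favouring the arm with more deaths fall from 25–27% to about 0.1%. Results against it rise from about 0.1% to 27–29%. With equal mortality the test stays near 5%.

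**The case against.** The plan is not blind to death. It requires survivor-only results beside the whole-sample ones. Death before discharge gets Kaplan-Meier curves and crude and adjusted Cox models (SAP 5.1.1), deaths are counted by arm (SAP 5.4), and death is a stopping outcome (SAP 2.3). Survival without BPD and survival without CLD are separate endpoints. A mortality gap large enough to distort stay would be visible in the same report. Observed days in all randomised infants is also a legitimate while-alive or resource-use quantity, and replacing it with a death-ranked outcome changes the question.

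Most of this stands, and it limits how serious the point is. It does not repair the whole-sample test. The survivor-only version conditions on a post-randomisation outcome, and nothing says which of the two results governs if they disagree. A separate mortality result warns a careful reader but leaves a misleading superiority p-value in place.

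The documents do not support four stronger readings that a reader might infer:

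- That all three durations are biased alike. Ventilation days are not, for the reason shown in the working.
- That the SAP states deaths are scored as short durations. It does not; this follows from the while-alive wording and the absence of any other rule.
- That a large distortion is to be expected. It needs a mortality difference between arms, and the documents give no basis for assuming a doubling.
- That the survivor-only test must be dropped. Given the other planned analyses, that is a preference.

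**Conclusion.** The concern holds for hospital stay and respiratory-support days. As written, the whole-sample comparison can favour the arm with more deaths when survivors do equally well in both arms. The default t-test is the more exposed for hospital stay; for respiratory support both tests are affected to a similar degree. The direction follows from the SAP's own wording, but the size depends on assumed survivor durations, times of death and the mortality gap. It is material at 10% vs 20%, modest at 10% vs 15%, slight at 10% vs 12%, and absent when mortality is equal. Using 10% for death to discharge in the lower-mortality arm is itself an assumption, because the protocol's 10% refers to death before 120 hours.

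These are secondary endpoints. The primary conclusion and the sample size are unaffected. The change should be made because it is cheap and removes a result that could contradict the mortality finding.

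**What to change.** In SAP 5.1.1, for the whole-sample comparison of hospital stay and of respiratory-support days, replace the t-test and difference in means with one Mann-Whitney test. In it, all infants who die before discharge share a rank worse than any survivor, including survivors censored under protocol 11.4. Changing only the Mann-Whitney fallback would leave the default test and the difference in means untouched. The same coding may be used for ventilation days for consistency.

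Keep observed days in all infants and survivor-only durations, label both as supportive, and present them beside mortality by arm.

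The cost is a sentence or two, a recode, and an entry in SAP section 6, because protocol 14.5.2 also names the t-test first. If the database is already locked, protocol 14.10 requires the change to be described and justified in the final report.

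The downside is that the ranked outcome mixes death with duration, so a significant result may reflect mortality alone. In the scenarios above with identical survivor stay, that is the whole source of the 27–29%. The report should say so.
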